### Statistical analysis

The statistical analysis will follow the example of Fournier et al. [22]. The continuous outcome (QIDS-C) will be analyzed with hierarchical linear models (HLM; nested random effects). The difference (T0-T2) will be controlled for baseline (T0) severity. Moderator and mediator analyses will be conducted according to Kraemer et al. [41]. The analysis of categorical outcome (remission classes) will be conducted with categorical regression with methods of optimal scaling (SPSS-CatReg) [42]. The identification of predictors with SPSS-CatReg is based on boot-strapping procedures or on the “Least Absolute Shrinkage and Selection Operators” [42]. For the HLM we will adapt the example of Fournier et al. [22] restricting the degrees of freedom of the selection of predictors in a hierarchical process.

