### Sample size calculation

The power calculation is based on assumptions about differences in the frequencies of remissions by treatment setting, the difference of means on the outcome measure, attrition and loss of cases due to mismatches. Given the probability of remission was p=0.30 for treatment A and p=0.45 for treatment B, then for equal *N* in each group, α = .05 and (1-β) = 0.80, the required sample size is *N* =180 (each group; calculated with PASS2008). For a standardized difference of *d* = 0.2 (small effect size) and α = .05 and (1-β) = 0.80, the required sample size is *N* = 200. With an attrition rate of 10% and loss due to mismatches of 20% (matching samples for research question II), the total sample size should be increased to *N* = 300 per group. Including covariates, subgroups and nesting (HLM) will help to increase the precision of models.

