### Methods against bias

To compare inpatient and day clinic samples, a parallelization according to known predictors of outcome [14] will be conducted: (1) Gender [m;f], (2) age [<40; >=40: mean age in previous studies], (3) number of additional axis-I diagnoses [<2; >=2], (4) number of previous episodes of major depression [0; <=2; >2] and (5) duration of the recent episode of MDE [<6 months; 6–24 mo >24 mo]. Criteria (1) to (3) will be matched 1:1; criteria (4) & (5) are used as lenient criteria, to be matched 1:1 if possible, otherwise the extremes may not be matched together. We expect a loss of about 20% due to “mismatches”, missing data and patients dropping out of the study.

Antidepressant medication, the initial score of the QIDS-C and the number of psychotherapy sessions following discharge will be controlled for in the final analysis. At the end of the study, patients screened and not taking part and patients taking part in the study will be compared, as well as patients dropping out of the study with those completing the study.

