To study inpatient and day hospital treatments can be seen as a problematic task, as treatments consist of multiple therapeutic elements, are provided by different treatment teams and hospitals are embedded in different environments. We can only try to reduce bias as good as possible. To control for centre effects, each hospital has to recruit a minimum of 35 patients in each setting. Treatment components will be documented in detail (sort, duration, frequency), although in a pilot study we found treatment programs to be quite comparable in dose and composition of elements, due to German standards for psychosomatic clinic programs. We will take the nesting of data (settings, clinics) into consideration by using complex statistic methodology. But we cannot rule out that the fact of taking part in a study influences treatment course and has some sort of impact.

In terms of dropping out of the study, we expect rates to be low, as there are much more advantages for agreement to participate compared to a refusal: Patients will get in-depth diagnostic assessments and allowances for filling in the questionnaires or taking part in follow-up assessments (20€ for each time point of measurement). Furthermore, depressed patients usually are a group of patients with a comparably high compliance rate.

The principal investigators and participating centers are experienced in the conduction of studies and all hospitals provide the usual standard care of psychosomatic centres. Most of the hospitals have been involved in the preceding pilot study [5,21].

Overall, we think this study will provide important data on the treatment of depression in the German health care system and help to tailor treatment programs to the needs of different subgroups of patients.

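### The model named for the matched setting comparison includes neither the pairs nor the matching factors; if pair members' outcomes are positively correlated, the standard error will be somewhat too large

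*Protocol article*

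**What the plan says.** Under Methods against bias, the protocol article introduces the matching for the setting comparison: "To compare inpatient and day clinic samples, a parallelization according to known predictors of outcome". It then fixes the rule: "Criteria (1) to (3) will be matched 1:1; criteria (4) & (5) are used as lenient criteria". The strict criteria are gender, age below 40 or not, and fewer than two additional axis-I diagnoses or not. The lenient ones are previous depressive episodes and duration of the current episode, each in three classes.

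The model is described in three places:

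- **Statistical analysis:** "The continuous outcome (QIDS-C) will be analyzed with hierarchical linear models (HLM; nested random effects", and "The difference (T0-T2) will be controlled for baseline (T0) severity". For the remission classes: "The analysis of categorical outcome (remission classes) will be conducted with categorical regression with methods of optimal scaling (SPSS-CatReg".
- **Discussion**, on the levels of nesting: "We will take the nesting of data (settings, clinics) into consideration by using complex statistic methodology".
- **Methods against bias**, on covariates: "Antidepressant medication, the initial score of the QIDS-C and the number of psychotherapy sessions following discharge will be controlled for in the final analysis".

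Sample size calculation adds a general remark: "Including covariates, subgroups and nesting (HLM) will help to increase the precision of models". None of these places names the matched pair or any of the five matching factors as a model term.

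**The concern.** The design of the comparison and the model named for it do not line up. Patients are selected into the comparison through five factors that the article itself regards as prognostic. Members of a pair should then have somewhat similar outcomes. A model that treats them as independent, given clinic and setting, does not credit that similarity in the standard error of the setting contrast. Intervals come out wider than the design warrants, the test is conservative, and a real difference between settings is a little easier to miss. The Background already reports comparable outcomes in earlier studies, so a null result would be readily taken as confirmation.

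There is a second, smaller consequence. Two of the five factors are matched only leniently, so some imbalance on them can remain. A model without them leaves it unadjusted.

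**Working it through.** **The article's own figure.** Sample size calculation gives N = 200 for d = 0.2, α = .05 and power 0.80. For two independent groups, two-sided, n = 2 × ((1.96 + 0.84)/0.2)² ≈ 393 per group (310 one-sided). So 200 does not reproduce as an unpaired calculation. It is close to a paired test with d taken on the within-pair difference, ((1.96 + 0.84)/0.2)² ≈ 197 pairs (199 with the t distribution). A baseline covariate correlated about 0.70 with the outcome would also bring 393 down to about 200. The article does not say how 200 was obtained. What matters here is that the contrast has little precision to spare.

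**Inputs.**

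- Pairs: 300 × 0.9 × 0.8 = 216, from the 10% attrition and 20% mismatch loss under Sample size calculation. Methods against bias gives about 20% loss in all, hence 300 × 0.8 = 240.
- Effect: d = 0.2. α = .05, taken as two-sided because sidedness is not stated.
- Within-pair correlation ρ: not in the document, so a range is assumed. It means the correlation left after baseline adjustment.

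**Formulas**, in units of the outcome SD:

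- SE ignoring pairs = √(2/n) = √(2/216) = 0.096
- SE using pairs = √(2(1−ρ)/n)
- Ratio = 1/√(1−ρ), which does not depend on n
- Power with pairs = Φ(0.2/SE_pair − 1.96)
- Power ignoring pairs = Φ((0.2 − 1.96 × SE_ign)/SE_pair)
- Type I error ignoring pairs = 2(1 − Φ(1.96 × SE_ign/SE_pair))

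Example, ρ = 0.20: SE_pair = √(1.6/216) = 0.0861 and the ratio is 1/√0.8 = 1.118. Power with pairs = Φ(2.32 − 1.96) = 0.64.

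| Assumed ρ | SE excess | 95% half-width, ignoring / using pairs | Power, ignoring / using pairs | Type I error, ignoring pairs |
|---|---|---|---|---|
| 0 | 0% | 0.189 / 0.189 | 54.7% / 54.7% | .050 |
| 0.02 | 1.0% | 0.189 / 0.187 | 54.8% / 55.5% | .048 |
| 0.05 | 2.6% | 0.189 / 0.184 | 54.8% / 56.8% | .044 |
| 0.10 | 5.4% | 0.189 / 0.179 | 55.0% / 59.1% | .039 |
| 0.20 | 11.8% | 0.189 / 0.169 | 55.3% / 64.2% | .028 |

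The power figures leave out any gain from the baseline covariate, so they show the size of the gap rather than the trial's actual power.

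**Do factor covariates do the same job as pairs?** A simulation (216 pairs, 4000 runs per scenario) let the five factors explain 0, 5, 10 or 20% of outcome variance, with exact matching on all five. The mean SE ignoring the matching was 0.096 throughout. With pairs it was 0.096, 0.094, 0.091 and 0.086, and with the factors as covariates it was the same to three decimals. The sampling SD of the point estimate was unchanged by these terms; only the reported SE moved.

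**When the direction changes.** If the factors act in opposite directions in the two settings (10% of variance, assumed), the SE ignoring pairs was 0.096 against a true SD of 0.101, with coverage of 93.8%. There the pair-based SE was right (0.101), while main-effect covariates left it at 0.096.

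**The case against.** The strongest reply is that this is a condensed article whose analysis plan is not shown. The text excludes no pair or stratum term. The three named covariates are not said to be the only ones, the sample size section speaks of covariates in general, and the HLM will select predictors, among which the matching factors are natural candidates. That stands as far as it goes: nobody can say from the article that the final model will omit them. But a general reference to covariates names no matching factor, and data-driven selection does not guarantee that these terms enter the setting contrast. Where the article does list what is controlled, the factors are absent.

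The second reply is that the matching is there to limit bias, and that benefit survives. This is correct. A reader might infer that the matching is wasted or that the estimate is distorted. The document supports neither: no precision gain is claimed for the matching, and under positive correlation the fault is in the cautious direction.

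The third reply is that the effect is small. This is largely right. Strict matching forms only 2 × 2 × 2 = 8 cells, two factors are lenient, and baseline QIDS-C is already adjusted, so ρ is probably low.

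A reader might also infer that a nested model cannot hold the pairs because they cross clinics. The article does not say whether matching is within or across clinics, so that inference is not available.

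**Conclusion.** The point holds in a modest and conditional form. The setting comparison is matched on five factors, and the model structure and covariates that the article names contain neither the pairs nor those factors. If ρ is positive, as the choice of prognostic matching factors implies, the reported SE of the setting contrast is about 1% to 5% too large for ρ of 0.02 to 0.10, and 12% too large at 0.20. The corresponding loss of power at 216 pairs and d = 0.2 is about 1 to 4 percentage points, and about 9 at 0.20. All of this rests on an assumed ρ and on a model run as named. It vanishes at ρ = 0 and can reverse if the factors act oppositely in the two settings.

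Two stronger readings are tempting. One is that the intervals are simply too wide, by a large amount; that needs a correlation near 0.5, for which the document gives no basis. The other is that N = 200 shows a paired test was intended; the figure fits that, but baseline adjustment could yield it too. The shortfall of 200 against 393 is a separate matter, which the pair term would not cure at plausible ρ: 354 pairs would be needed at ρ = 0.10.

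**What to change.** For the matched comparison, state in the analysis section that the HLM will include the five matching factors, in the classes used for matching, as prespecified fixed covariates alongside clinic and setting, outside the predictor selection. A random effect for matched pair is an acceptable alternative, provided the pair identifier is kept in the data set. Include the same five factors in the remission model. The covariates also adjust for imbalance left by the two leniently matched factors.

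The cost is a sentence or two and no new data. Main effects for three two-level and two three-level factors use 3 × 1 + 2 × 2 = 7 degrees of freedom, out of 2 × 216 = 432 patients. With the pair option, the pair variance may be estimated near zero, in which case the result is essentially that of the model without it.

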### Measurement time points

Time points of measurement will be the time point at admission (T0), at discharge (T1), a three months follow-up (T2) and a 12 months follow-up (T3). Data will include a detailed assessment on different levels: symptomatology (characteristics of depression and co-morbid conditions), general disturbance and quality of life, aspects of personality, interpersonal problems and a further aspects that has been identified to influence the course of depression: traumatic childhood experiences. Variables will be grouped into classes of possible predictors. A combination of self-report and assessments by independent, trained research assistants will be used (see Table 2).

**Table 2 T2:** Instruments used the INDDEP study

**Time point of measurement**	**Outcome/Variables**	**Patient**	**Research assistant**
		**(self-report)**	**(expert rating)**
**T0 **(admission)	Depressive symptomatology:	QIDS-SR	QIDS-C, SKID-I
	Co-morbidity		SCID I + II
	Personality, interpersonal problems, mode of coping:	IIP-32, DEQ, DAS	
	Overall disturbance and functioning:	SCL-90-R	SOFAS
	Social support:	F-SozU K-14	
	Quality of Life:	SF-12	
	Traumatisation:	CTQ	
**T1 **(discharge)		QIDS-SR	QIDS-C
		SCL-90-R	SOFAS
		IIP-32	
**T2 **(3-months Follow-up) and **T3 **(12-months Follow-up)		QIDS-SR	QIDS-C, LIFE-Interview
		SCL-90-R	SOFAS
		SF-12	
		IIP-32	

QIDS-SR = Quick Inventory of Depressive Symptoms, self-report form [23], QIDS-C = expert rating; SCID-I and SCID-II=Structured Clinical Interview for DSM IV axis I and II [24,25]; SCL-90-R = Symptom-Check-List 90-R [26]; DAS = Dysfunctional Attitudes Scale [27,28]; DEQ = Depressive Experiences Questionnaire [29,30]; SOFAS = Social and Occupational Functioning Assessment Scale [31]; IIP-32 = Inventory of Interpersonal Problems, 32-item version [32,33]; F-SozU K-14 = Fragebogen zur sozialen Unterstützung, 14-item version [34]; SF-12 = Fragebogen zum Gesundheitszustand (quality of life) [35]; CTQ = Childhood Trauma Questionnaire [36,37]; LIFE-Interview = Longitudinal Interval Follow-up Evaluation [38].

Note: Additionally assessed at all time points of measurement: pharmacological treatment, somatic diagnoses; at T0: previous treatment for depression; at T1: documentation of treatment received (dose, components); T2 and T3: further outpatient treatment, days of sick leave, number of contacts to health care system.

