### Outcomes

The Quick Inventory of Depressive Symptomatology QIDS-C (expert rating) is chosen as the main outcome criterion. The QIDS is a 16-item version of the Inventory of Depressive Symptomatology (IDS), which shows high correlations with other instruments for the measurement of depressive symptomatology [23]. It´s a common, internationally used, licence-free instrument which has a self-report and an expert rating form [23]. The QIDS was chosen as its total score is also used as the main outcome criterion in a large trial on outpatient psychotherapy for chronic depression that is currently conducted in Germany (“LAC-study”, [39]).

We aim to assess outcome dimensionally (change on the QIDS-C score from admission to the three-months follow-up) as well as categorically: a symptom reduction < 20% is defined as “no effect”, a symptom reduction between 20% and 50% as modest change, a symptom reduction of > 50% as partial remission and a symptom reduction of 100% as complete remission (falling below the cut-off value of depression of the QIDS-C) [3,40].

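### The setting comparison rests on one T0-T2 QIDS-C difference, so followed as written it rests on patients seen at T2; a repeated-measures form of the planned HLM would reduce attrition bias at little cost

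*Protocol article*

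**What the plan says.** - **Outcome.** Under Outcomes, the "QIDS-C (expert rating) is chosen as the main outcome criterion", and its dimensional form is "change on the QIDS-C score from admission to the three-months follow-up".
- **Model.** Under Statistical analysis, the continuous outcome "will be analyzed with hierarchical linear models (HLM; nested random effects"), and "The difference (T0-T2) will be controlled for baseline (T0) severity". The Discussion names the levels: "We will take the nesting of data (settings, clinics) into consideration". Visits are not named as a level.
- **Ratings available.** Measurement time points lists admission (T0), then "at discharge (T1), a three months follow-up (T2) and a 12 months follow-up (T3"). Table 2 has the QIDS-C at all four.
- **Drop-out.** Methods against bias forecasts a loss of about 20% from mismatches, "missing data and patients dropping out of the study". It also plans to compare drop-outs with completers. Sample size calculation treats the losses separately: "With an attrition rate of 10% and loss due to mismatches of 20" per cent.
- **Covariates.** Methods against bias also adjusts the final analysis for the number of psychotherapy sessions after discharge. The note to Table 2 records further outpatient treatment only at T2 and T3.

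**The concern.** The form of the outcome determines who can contribute. A T0-T2 difference exists only for patients rated at T2, so an analysis that follows this text begins from the patients who came back. Adjusting for T0 protects that analysis only if drop-out depends on setting, T0 severity and the other covariates in the model. It does not protect against drop-out driven by how the patient responded between admission and discharge. The T1 rating carries that information and is already collected, but it has no stated use here.

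This matters more than in a randomised trial. The settings are not allocated at random, and the comparison relies on matching to make the samples alike. Drop-out related to response and setting can undo that balance after admission. The planned comparison of drop-outs with completers would show the problem without changing the estimate. The planning effect is also small (d = 0.2), so a modest bias is a sizeable fraction of it.

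**Working it through.** **1. The plan's own figures.** The inputs from Sample size calculation are alpha 0.05, power 0.80, remission 0.30 versus 0.45, d = 0.2, 10% attrition and 20% mismatch.
- Remission: the two-sided formula with continuity correction gives 176 per group, so the stated 180 is reproduced.
- d = 0.2: two independent groups need 2 × ((1.96 + 0.84)/0.2)² = 393 per group. The stated 200 is reproduced only as matched pairs, ((1.96 + 0.84)/0.2)² = 197, a reading the article does not state. This is a separate matter and is used here only to choose power formulas.

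**2. How many remain.** The two sections differ on what the 20% covers, and the timing of matching is not stated. Three readings are possible:
- 20% includes drop-out: 300 × 0.8 = 240 per setting.
- 10% attrition and 20% mismatch, counted per patient: 300 × 0.9 × 0.8 = 216 per setting.
- Matching first, with every pair that has a drop-out removed: 300 × 0.8 × 0.9 × 0.9 = 194 pairs.

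**3. Bias.** Let p be the share lost in a setting and g the gap, in SD after adjustment for T0, by which drop-outs are worse than completers. The completers' mean is too favourable by p × g, so the setting contrast is off by the difference of p × g between settings. If p and g are equal in both settings, the contrast is not biased. No value of g, and no split of attrition by setting, stands in the article. Under assumed values:
- p = 15% versus 5% (average 10%, the plan's rate), g = 0.5 in both: (0.15 − 0.05) × 0.5 = 0.05 SD, and 0.05/0.2 = 25% of d.
- p equal in both settings, g differing between them by 0.2, 0.5 or 1 SD: 0.02, 0.05 or 0.10 SD at p = 10%, and 0.04, 0.10 or 0.20 SD at p = 20%.

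**4. Power.** Start from 240 matched patients per setting with 10% missing T2, so 216 complete cases. If T1 and T3 explain a share R² of T2 variance, and a share s of drop-outs have such ratings, the effective number is about 216 + 24 × R² × s. With assumed R² of 0.25 to 0.50 and s of 0.5 to 1, this is 219 to 228. Power is Φ(0.2√(n/2) − 1.96) for two groups and Φ(0.2√n − 1.96) for pairs. Remission uses the normal approximation and is shown for scale only.

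| Basis | Two-group d = 0.2 | Paired d = 0.2 | Remission |
|---|---|---|---|
| 194 complete pairs | 50.5% | 79.6% | 86.6% |
| 216 complete cases per setting | 54.7% | 83.6% | 89.9% |
| Repeated measures, 219 to 228 | 55.3 to 57.0% | 84.1 to 85.5% | 90.3 to 91.4% |
| 240, nothing lost | 59.1% | 87.3% | 92.7% |

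The gain over complete cases is 0.4 to 2.3 points. Over complete pairs it is about 4 to 6 points (3.7 to 6.5), but only if whole pairs are lost.

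**The case against.** The strongest reply is that the article states no complete-case rule. Allowing for attrition in the sample size is routine and does not commit the analysis to completers. Missing-data handling may be in the full protocol or the SAP, and the HLM follows a cited example that is not at hand. Baseline-adjusted change at a fixed visit is a standard estimator. The article expects little drop-out and pays patients for each assessment. The predictor analysis uses the whole sample, so matching concerns only the setting comparison.

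Much of this stands. A reader might infer that the plan discards patients with T1 or T3 ratings. It does not say so; those ratings only have no stated use in this contrast. A reader might also infer that drop-outs break matched pairs and leave fewer than the required 200. The article says neither when matches are formed nor that the analysis is paired. The figure of 194 is one of three readings, the others being 216 and 240, and even at 194 the paired power is 79.6%. The bias inputs are assumed.

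A further objection is practical. A patient with T1 only would lack the planned covariate for sessions after discharge and would still be excluded under a repeated-measures model. This is correct, and the fix has to deal with it.

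The reply does not remove the core. The single T0-T2 difference is written in both Outcomes and Statistical analysis, so the point is about a stated choice and not about an absent imputation method.

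**Conclusion.** The point holds as a recommendation about a stated analysis choice. Followed as written, the setting comparison rests on patients rated at T2, and the stated check on drop-out cannot correct it. The case rests on bias: 0.05 SD, or a quarter of d = 0.2, under one assumed scenario, and 0.02 to 0.20 SD across the others shown. There is no bias in the contrast if attrition and the gap are the same in both settings. Power is a minor argument, because the recoverable part is about 0.4 to 2.3 points over complete cases at 10% attrition and the target of 300 already allows for loss. The documents do not support saying that the plan prescribes a completers-only analysis, breaks pairs, or falls below its own requirement.

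**What to change.** Reword the analysis of the setting comparison as follows:

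- Form matches from T0 data only, among all enrolled patients, by setting at admission.
- Fit the planned HLM to QIDS-C at T1, T2 and T3, with patient as a further level, T0 as covariate and setting by time. Keep the setting contrast at T2 as primary, so the question does not change.
- Keep the baseline-adjusted T0-T2 analysis in completers as a sensitivity check, alongside the planned comparison of drop-outs with completers.
- Move the adjustment for psychotherapy sessions after discharge to a secondary analysis. It is known only from T2 and T3, and in the primary model it would exclude patients with T1 only.

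The cost is wording and slightly more modelling; no new ratings are needed. The result then relies on data being missing at random given T0, the observed later ratings and the covariates. Patients with no rating after admission, which may include some who leave before discharge, are still not covered, and their number should be reported by setting.

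### For the remission classes only single-level CatReg is named: it cannot carry the promised centre nesting and does not estimate the 0.30 vs 0.45 remission difference used in the sizing

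*Protocol article*

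**What the plan says.** The Statistical analysis section makes two explicit choices. The continuous QIDS-C is to be analysed with a hierarchical linear model with nested random effects. For the classes it says: "The analysis of categorical outcome (remission classes) will be conducted with categorical regression with methods of optimal scaling (SPSS-CatReg". It then describes CatReg as a means of identifying predictors, by bootstrap or LASSO. It names no other method for the classes and no comparison of remission proportions between settings.

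Two other places bear on this choice:

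- The Discussion gives an undertaking that is not limited to one outcome: "We will take the nesting of data (settings, clinics) into consideration by using complex statistic methodology".
- The Sample size calculation has a remission criterion: "Given the probability of remission was p=0.30 for treatment A and p=0.45 for treatment B". With groups of equal size, a 5% alpha and 80% power, it arrives at 180 patients in each. It has a second, continuous criterion, a small standardised effect of 0.2, for which it gives 200. It mentions nesting only in connection with HLM: "Including covariates, subgroups and nesting (HLM) will help to increase the precision of models".

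The Outcomes section defines four classes by percentage reduction and labels two of them remission, one partial and one complete. The sizing does not say which of the two the 0.30 and 0.45 refer to.

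**The concern.** CatReg assigns scores to categories so as to maximise fit and then runs an ordinary single-level regression. Two things follow.

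First, patients treated in the same unit are handled as independent, apart from whatever a centre predictor might absorb. The continuous coding of the scale gets a nested model and the categorical coding does not, although the Discussion makes no such distinction.

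Second, a setting coefficient on a four-class outcome with data-chosen scores is neither a difference in proportions nor an odds ratio. If setting is entered, the result is a test of association with the rescaled classes. It cannot be read against the 15-point difference in the sizing. The comparison of settings on remission, which belongs to the study's second step, is left without a method that fits it.

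At stake are the error rate of any statement about setting drawn from the categorical analysis, and whether the study reports the remission contrast for which it calculated power.

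**Working it through.** **Inputs.** Remission 0.30 vs 0.45, alpha 0.05, power 0.80, stated N of 180 per group, 300 recruited per group, and losses of 10% and 20% (Sample size calculation: "With an attrition rate of 10% and loss due to mismatches of 20"%). Seven centres (Study centers). At least 35 patients per setting in each centre (Participants), so every centre supplies both settings. Assumptions of mine: a two-sided test, because sidedness is not stated, and an intraclass correlation rho of 0.01 to 0.05, because the article gives none.

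**Step 1: reproduce 180.** For two independent proportions with mean 0.375:

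n = [1.96 × √(2 × 0.375 × 0.625) + 0.842 × √(0.30 × 0.70 + 0.45 × 0.55)]² / 0.15² = 163 per group.

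With the continuity correction n becomes 176, within 3% of the stated 180. The figure is therefore consistent with an ordinary comparison of two independent proportions, with no clustering term. That comparison does not appear in the Statistical analysis section.

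**Step 2: patients per unit.** 300 × 0.9 × 0.8 = 216 per group. Seven centres by two settings give 14 units, and 432 / 14 = 30.9 patients per unit.

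**Step 3: variance of the setting contrast.** On a standardised scale with total variance 1, an unclustered analysis uses 2/216. The true variance depends on where the clustering lies.

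- All clustering common to the two settings of a centre: the centre effect cancels from the contrast, the true variance is 2(1 − rho)/216, and the ratio to the unclustered variance is 1 − rho.
- All clustering specific to the centre-by-setting unit: the true variance is 2(1 − rho)/216 + 2rho/7, and the ratio is 1 + rho(216/7 − 1).

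The true error of a nominal 5% test is 2[1 − Φ(1.96/√ratio)].

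| rho | Ratio, all common | Error | Ratio, all unit-specific | Error |
|---|---|---|---|---|
| 0.01 | 0.99 | 4.9% | 1.30 | 8.5% |
| 0.02 | 0.98 | 4.8% | 1.60 | 12.1% |
| 0.05 | 0.95 | 4.4% | 2.49 | 21% |

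If half of rho is common and half unit-specific, the ratio is (1 − rho) + (rho/2)(216/7). That is 1.14 at rho = 0.01 and 1.72 at rho = 0.05, with errors of about 6.7% and 13.5%.

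**Step 4: which sizing criterion binds.** Taking the stated numbers as they stand, 200/(0.9 × 0.8) = 278 and 180/(0.9 × 0.8) = 250. The continuous criterion is the larger of the two.

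**The case against.** The strongest reply has four parts.

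- *The primary outcome is covered.* The abstract names the QIDS total score as the primary criterion, and its continuous analysis is nested. This is correct, and it limits the weight of the point. It does not supply a method for the remission contrast.
- *Centre may be in the CatReg model.* The article does not list the model terms, and centre could enter as a nominal predictor. A reader might infer that the plan ignores centre altogether, and the text does not support that. But a centre predictor absorbs only what both settings of a centre share. Variation between settings within a centre, the part that inflates error, would stay in the residual.
- *Setting may be a CatReg predictor.* A reader might infer that remission by setting goes wholly untested. That is also too strong, since association with the scaled classes could be tested. What is missing is an estimate or direct test of the sized difference.
- *CatReg is there to find predictors.* That is its stated role, and it suits the first, exploratory step. It gives no reason to leave the setting comparison to the same tool. Nor is it an error that two selection procedures on two codings of one scale may produce different predictor lists. The article plans both views deliberately.

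This is not a matter of detail left to a fuller document: the article names a specific procedure for the remission classes, and that procedure does not fit the setting contrast.

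**Conclusion.** The point holds in limited form. The only method named for the remission classes has no random effects, so it cannot carry the centre and centre-by-setting nesting that the Discussion promises to consider. It also does not estimate or directly test the 0.30 vs 0.45 difference.

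A reader might infer that the setting test is bound to be anti-conservative. The documents do not support that. Each centre recruits both settings, and under a purely common centre effect the unclustered test is slightly conservative. Over rho of 0.01 to 0.05, the true error of a nominal 5% test runs from about 4.4-4.9% at one extreme to about 8.5-21% at the other. These figures rest on an assumed rho, equal unit sizes, the stated losses and a normal approximation. The split between common and unit-specific variation is unknown.

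A reader might also infer that the study's size rests on the remission difference. It is one of two criteria, and the stated 200 for d = 0.2 exceeds the stated 180.

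**What to change.** For the setting comparison, state which single class or cut from the Outcomes section counts as remission. Analyse it with a logistic mixed model that has the same centre and centre-by-setting structure and the same covariates as the HLM, and that respects the matching described under Methods against bias. Report the odds ratio and the difference in remission proportions, each with a confidence interval. A proportional-odds mixed model on the ordered classes can be added. Keep CatReg with bootstrap or LASSO, labelled as exploratory identification of predictors.

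The cost is a change of wording and standard software, with no new data. Intervals may be somewhat wider, and seven centres give limited information on the variance components. The loss of power should be acknowledged. With 216 per group, power for 0.30 vs 0.45 is about 0.90 under independence. If all clustering is unit-specific, dividing 216 by the ratios in the table leaves effective group sizes of 166, 135 and 87 for rho of 0.01, 0.02 and 0.05, with power of 0.81, 0.72 and 0.53.
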